#### Plans to promote participant retention and complete follow-up {18b}

Participants will be contacted through telephone; after 3 unsuccessful attempts to reach the subject, a registered mail will be sent to the subject to indicate the need for a follow-up appointment. If these communications are unsuccessful, the subject will be considered lost to follow-up.

Data of withdrawn subjects, collected up until the point of withdrawal, will be preserved and used in the applicable analyses. The reasons for withdrawal will be compared between treatment arms, to assess potential bias in the analysis. The reason for discontinuation must be recorded in the source documentation and the e-CRF. Possible reasons for discontinuation of participation may include, but are not limited to, the following reasons:Subject decides to withdraw from the studyAdverse eventsLost to follow-up

#### Data management {19}

An electronic data capturing (EDC) system will be used to collect data on a secure, Internet-based electronic case report form (e-CRF), and image transfer software. The principal investigator (PI) or his/her designee at the clinical site will perform primary data collection by entering the data into the e-CRF. Only the PI or other predesignated personnel will be authorized to enter data using their unique login credentials. Each user access to the system will be tracked so that all data operations can be monitored and verified.

The e-CRF will be completed on a continuous basis starting from the point of enrollment to final follow-up.

A critical quality control shall be performed for the first 2 subjects by the sponsor’s designated data management team and queries issued where needed. Such queries must be reviewed by the monitor prior to alerting the site personnel to answer them.

After the monitor has done the source document verification and obtained satisfactory answers to eventual queries from the site, a full quality control shall be performed on the monitored data throughout the clinical investigation by the designated data management team and queries issued where needed. This process will be repeated till the end of the clinical investigation so as to allow for a timeline freezing of the data base for statistical analysis.

#### Confidentiality {27}

The investigator must ensure that subjects’ anonymity will be maintained. On e-CRFs or other documents submitted to the sponsor, subjects should not be identified by their names, but by the subject number. The investigator must keep a subject identification code list showing the enrolment number, the subject’s name, date of birth, and address or any other locally accepted identifiers. All information to be sent to the sponsor concerning patients and their participation in the study will be considered confidential. All data will be processed without identifiable reference to the individual patient.

#### Plans for collection, laboratory evaluation, and storage of biological specimens for genetic or molecular analysis in this trial/future use {33}

The collection and evaluation of laboratory tests will be performed according to the standard procedures per study site. The following laboratory tests may be applicable to participants in this this trial: pregnancy test, CRP, leucocytes, and β-2 transferrin test.

### Statistical methods

#### Statistical methods for primary and secondary outcomes {20a}

The primary analysis set will consist of a modified intention to treat analysis (mITT). Modified intent-to-treat (mITT) analysis set is a subset of ITT analysis set and will consist of all enrolled subjects (subjects who have signed the ICF, meet all inclusion criteria, meet none of the exclusion criteria and the investigational/control device has contacted the subject’s dura) with evaluable data for the primary endpoint.

The primary endpoint will be evaluated for statistical significance based on the Wald method for difference of proportions. If non-inferiority is met a one-sided significance level of 5%, the difference in success rates will also be evaluated for superiority at a one-sided significance level of 5%.

The primary endpoint will also be summarized by investigational site and cranial procedure type. Interactions of treatment and site/procedure type may be examined graphically or using logistic regression with success rate at day 90 as the response variable, and the study center (or procedure type), treatment group, and study center (or procedure type) by treatment group interaction as predictor variables in the model. If the results of the test show evidence of heterogeneity across sites/procedure types (i.e., *p*-value<0.15), then the treatment/procedure type effect will be evaluated further to identify any confounding factors.

All safety analyses will be based on subjects in the intention-to-treat (ITT) analysis set. The ITT analysis set will consist of all enrolled subjects (subjects who have signed the ICF, meet all inclusion criteria, meet none of the exclusion criteria, the investigational/control device has contacted the subject’s dura). Results based on the ITT analysis set will be analyzed according to each subject’s randomization assignment.

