#### Sample size {14}

“Success” was defined as absence of the composite endpoint. The success rate of the investigational product was set similar to that of the control devices combined. The combined success rate of the control devices was determined at 91%, based upon a comparative study of the two devices [6]. The non-inferiority margin was set at 10%, this was accordance with the design used by the control devices [6] and believed to be clinically acceptable. The power of the study is 80%, with a one-sided significance level of 5%. The expected rate of attrition is 10%. Under these assumptions, a total of 228 patients are required, 114 per arm.

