### Assignment of interventions: allocation

#### Sequence generation {16a}

The randomization schedule will be generated using an Internet-based computerized randomization program within the research management platform (RMP) and electronic data capturing system Staicy v2.33 (IQVIA MedTech, Danbury, USA). The RMP is fully validated and 21 CFR part 11 (and EU Annex 11) compliant. It is developed under an ISO27001 certified quality management system.

Patients will be stratified by study site and type of cranial surgery (craniotomy or craniectomy) in blocks of 4 and randomized (1:1) at the start of surgery.

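### The Wald test named for the primary non-inferiority comparison runs modestly above its stated one-sided 5% level; a score bound would hold it for about 2 points of power

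*Protocol article*

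**What the plan says.** The protocol article, section Statistical methods for primary and secondary outcomes {20a}, states that the primary endpoint is "evaluated for statistical significance based on the Wald method for difference of proportions". It applies a one-sided 5% level to non-inferiority and, once that is met, the same level to superiority. No continuity correction and no strata are mentioned for the test. Site and procedure type appear in that section in summaries and in optional interaction checks.

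Section Sample size {14} gives the design values:
- "The power of the study is 80%, with a one-sided significance level of 5" per cent;
- "The combined success rate of the control devices was determined at 91" per cent;
- "The success rate of the investigational product was set similar to that of the control devices combined";
- "The non-inferiority margin was set at 10" per cent;
- "The expected rate of attrition is 10" per cent;
- "a total of 228 patients are required, 114 per arm".

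Section {20c} restricts the primary analysis to available data, so about 90% of 114, or 102 to 103 per arm, should be evaluable. On randomisation, section Sequence generation {16a} says "Patients will be stratified by study site and type of cranial surgery (craniotomy or craniectomy) in blocks of 4".

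**The concern.** The Wald test divides the observed difference plus the margin by a standard error built from the two observed proportions. When success rates are close to 1, a sample that happens to show few device failures yields both a favourable difference and a standard error that is too small. The two errors reinforce each other, so the test rejects the inferiority hypothesis more often than its nominal level allows.

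The stake is the trial's main claim. The excess runs in one direction, towards declaring the patch non-inferior, and it adds to a level already set at one-sided 5%. It also grows if the control does better than planned.

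**Working it through.** **1. Reproduce the planned size.** Inputs from section {14}: success 0.91 in both arms, margin 0.10, one-sided 5% (z = 1.645), power 80% (z = 0.842).

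n per arm = (1.645 + 0.842)² × (2 × 0.91 × 0.09) / 0.10² = 6.185 × 0.1638 / 0.01 = 101.3, rounded up to 102.

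With 10% attrition: 102 / 0.90 = 113.3, rounded up to 114 per arm and 228 in total. This matches the article. It is the unpooled, uncorrected formula, which indicates that the uncorrected Wald test is meant.

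**2. Exact one-sided error at the margin.** Take two independent binomials with control success p and device success p − 0.10. At p = 0.91 and 102 per arm that is about 9 expected control failures (0.09 × 102 = 9.2) and 19 device failures (0.19 × 102 = 19.4). The test declares non-inferiority when

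(device rate − control rate + 0.10) / SE > 1.645.

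For Wald, SE uses the observed rates. For the Farrington-Manning score test, SE uses the maximum-likelihood rates constrained to differ by exactly 0.10. Summing the binomial probabilities over all rejecting outcomes gives, for 102 / 103 / 114 per arm:

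| Control success | Wald error | Score error |
|---|---|---|
| 85% | 5.11 / 5.23 / 5.14% | 5.07 / 4.97 / 5.13% |
| 88% | 5.27 / 5.22 / 5.21% | 5.02 / 5.06 / 5.09% |
| 91% (planned) | 5.55 / 5.34 / 5.45% | 4.98 / 5.10 / 4.93% |
| 95% | 5.90 / 5.80 / 5.89% | 5.10 / 4.89 / 4.59% |
| 97% | 6.22 / 6.71 / 6.22% | 4.94 / 4.70 / 4.38% |
| 98% | 6.66 / 7.34 / 6.66% | 4.65 / 4.42 / 4.30% |

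The result does not hang on one sample size. For every n from 95 to 117 per arm the Wald error exceeds 5%: 5.21 to 5.65% at 91%, and 5.64 to 6.46% at 95%.

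**3. Power at 91% in both arms.**

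| Evaluable per arm | Wald | Score |
|---|---|---|
| 102 | 80.5% | 78.5% |
| 103 | 80.4% | 78.4% |
| 114 | 84.1% | 81.2% |

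**4. Can it change the verdict?** Take 102 per arm, 9 control failures and 12 device failures, so success is 93/102 = 0.9118 against 90/102 = 0.8824 and the difference is −0.0294.

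- Wald: SE = √(0.8824 × 0.1176/102 + 0.9118 × 0.0882/102) = 0.0425. Lower bound = −0.0294 − 1.645 × 0.0425 = −0.0993, inside the margin, so non-inferiority is declared.
- Score: the constrained rates are 0.8336 and 0.9336, SE = 0.0444, z = 0.0706/0.0444 = 1.59, below 1.645, so it is not declared.

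The largest number of device failures that still passes, Wald against score, is 12 against 11 with 9 control failures at 102 per arm, and 13 against 12 at 114. With 5 control failures it is 9 against 8 and 10 against 9. At other counts, such as 10 control failures, the two methods agree.

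**5. Role of the strata.** A simulation of 19 sites × 2 procedure types, blocks of 4, 204 patients and 15,000 runs, at 91% control success, gave a Wald error of 5.5% with no stratum effects. It was 5.4% with modest effects (site SD 2 points, procedure type ±3 points) and 5.0% with strong ones (procedure type ±6 points); Monte Carlo SE was about 0.2 points. A separate simulation of 4,000 trials, with assumed site SD of 0.7 to 1.0 on the log-odds scale, gave mean SEs of 0.0397 unstratified against 0.0395 stratified by procedure type, and 0.0390 against 0.0387: gains of 0.5% and 0.8%. The stratum effects in both are assumptions; the article gives none.

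**The case against.** The strongest reply is that this is small. At the plan's own 91% the excess is 0.3 to 0.55 points, the sample-size formula and the test are consistent with each other, and the proposed change takes power below the stated 80%. That stands as a statement of size. It does not restore the stated level, and the discrepancy is always in the same direction.

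A reader might infer from the 97% and 98% rows that the real error is 6 to 7%. The documents do not support that as an expectation. The plan assumes 9% failures, the endpoint has five components, including leakage at raised PEEP and a volume threshold on MRI, and only patients who leak after primary closure are eligible. Nothing points to 2 to 3% failures.

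A reader might also infer that leaving site and procedure type out of the test is an error, or that it causes the inflation. Neither follows. Ignoring prognostic strata makes the test more conservative and can offset the excess, as step 5 shows. The article names no strata for the test, but it is condensed, and adjustment is commonly left to an analysis plan not shown here. With 19 × 2 = 38 cells and 228/38 = 6 patients per cell, an unstratified test is defensible.

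One could read the article's wording as a continuity-corrected Wald test. With a 1/n correction the error at 91% is only 3.4 to 3.7%. But power at 102 per arm would then be about 73%, and 228 reproduces only from the uncorrected formula, so this reading is unlikely.

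Finally, this is not the only confirmatory test, because superiority follows at the same level. The Wald superiority test has a smaller excess at 91% (5.2%).

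**Conclusion.** The point holds at modest size. The test named in section {20a} does not deliver the stated one-sided 5%: about 5.3 to 5.6% at the planned control rate and 5.8 to 5.9% at 95%, with a smaller excess at 85 to 88%. It favours declaring non-inferiority and can turn the verdict on a single patient at counts close to the planned ones. This rests on the uncorrected Wald test, 102 to 114 evaluable per arm in equal numbers, independent binomial outcomes without strong stratum effects, and a true difference exactly at the 10-point margin. The sample size of 228 is correct for the test as planned, and the handling of strata is not part of the fault.

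**What to change.** In section {20a} and in the analysis plan, replace the Wald test with the one-sided 95% Miettinen-Nurminen (or Farrington-Manning) score bound for the difference in success rates, judged against the same 10-point margin. The error is then about 4.9 to 5.1% at 91% and 4.6 to 5.1% at 95%. The score test is not exactly 5% either, but it stays close and errs low at the highest success rates. The same method can serve the follow-on superiority test.

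In section {14}, restate power as about 78% at 102 to 103 evaluable per arm, or 81.2% if all 114 per arm are evaluable.

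Optionally, stratify the bound by craniotomy or craniectomy, as randomised; the expected precision gain is 0 to 1% in SE. Do not use all 38 site-by-procedure cells: single-arm cells would drop out, and in simulation power fell by up to 2 points when the strata were not prognostic.

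The cost is a wording change, standard software and about 2 points of power, with no extra patients unless the sponsor wants to keep 80%. The article reports the trial as still recruiting, so the change should be dated and made before any comparison of outcomes by arm.

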#### Intervention description {11a}

The patient is electronically randomized for LIQOSEAL or control device on the day of surgery by trained personnel other than the operating surgeon.The assigned dural sealant is taken out of the freezer/storage and placed in a non-transparent box.First PEEP test (for safety).Dura mater is closed with the standard method of suturing.Hemostasis should be achieved.The dura mater surface is rinsed from particles with physiological saline and kept moist.Second PEEP test (CSF leakage confirmed).Surgeon is unblinded and the dural sealant is applied.For LIQOSEAL: the dry patch is cut into the required size and positioned with the white side against the sutured area of the dura mater and compressed for 2 min with a moist gauze.For Duraseal and Adherus: the hydrogels are applied aiming at the sutured area of the dura mater, holding the device 2–4 cm away, until a thin coating (1–2 mm) is formed.9.Third PEEP test (2 min after device implantation).10.Standard closure of cranial defect and soft tissue will then be undertaken per surgeon standard.

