#### Criteria for discontinuing or modifying allocated interventions {11b}

Once the patient is allocated to the control or interventional arm the patient can still be excluded from the study in case the intraoperative eligibility criteria are not met or in case the first PEEP test was not considered safe for the patient. Once the allocated intervention has been applied, this can be modified in case the patient reaches the primary outcome during the surgery (intraoperative CSF leakage at the third PEEP test). In such case, the neurosurgeon can undertake any actions deemed necessary to ensure optimal patient care in the situation.

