##### Intraoperative data

The device used and its size, LOT number, size of trepanation, any use of autologous material, and type of suture are recorded.

To determine the intraoperative CSF leak before and after the application of the device, the PEEP will be increased to 20 cmH2O for 20 s. First, this test will be performed before closure of the dura to determine safety for the postoperative intracranial field (control of hemorrhage, swelling or other potential adverse effects). Upon completion of the primary sutured dural closure and before the application of the sealant, the closure of the dura will be evaluated for CSF leakage by repeating the test. The patient is excluded if there is no leakage at PEEP of 20 cmH2O for 20 s. Two minutes after application of the device, the test will be performed for a third time to evaluate CSF leakage. All 3 PEEP elevations and application of the device will be recorded on video. A photograph will be taken before and after device application.

After the procedure, end users (surgeons, scrub nurses) will be invited to complete several closed-end questions regarding their user experience with LIQOSEAL.

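### The set called ITT is a treated set defined by an event after unblinding, so an eligible patient with a confirmed leak who receives no study device drops out of every planned analysis

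*Protocol article*

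**What the plan says.** All references are to the protocol article.

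- **Order of events.** The steps listed under Intervention description {11a} begin with allocation: "The patient is electronically randomized for LIQOSEAL or control device on the day of surgery by trained personnel other than the operating surgeon". Next come the first PEEP test, sutured closure and the second PEEP test. Only then, "Surgeon is unblinded and the dural sealant is applied". The third PEEP test comes 2 minutes after implantation.
- **Exclusion after allocation.** Criteria for discontinuing or modifying allocated interventions {11b}: after allocation, "the patient can still be excluded from the study in case the intraoperative eligibility criteria are not met", or if the first PEEP test was not considered safe. Intraoperative data (under {18a}): "The patient is excluded if there is no leakage at PEEP of 20 cmH2O for 20 s".
- **Analysis sets.** Statistical methods {20a} restricts ITT to subjects who have consented and satisfy all inclusion criteria, and who "meet none of the exclusion criteria, the investigational/control device has contacted" the dura. ITT subjects are analysed by randomised arm. The mITT set, which is primary, is a subset with evaluable endpoint data. All safety analyses use the ITT set. Methods for additional analyses {20b} adds a per-protocol analysis and an analysis of this same ITT set.
- **Blinding.** Sections {17a} and {17b} end the surgeon's blinding when primary dural closure is final; {11c} says much the same. None of the three mentions the second PEEP test.
- **Allocation.** Sequence generation {16a} stratifies by site and by craniotomy or craniectomy, "in blocks of 4 and randomized (1:1) at the start of surgery".

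**The concern.** An intention-to-treat set should be fixed by randomisation or, at the latest, by facts established before anyone who can influence membership knows the arm. Here membership depends on whether a device touched the dura, which happens when the surgeon already knows what is in the box. If a device is opened and found unusable, or is withheld, and no study device is applied, the patient leaves ITT, mITT and safety together.

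In a non-inferiority trial the direction matters. If such cases arise more often with the new patch, for reasons linked to its performance, leaving them out favours non-inferiority. The supplementary ITT analysis should be able to expose this, but it applies the same contact rule as the primary set and so shares its blind spot.

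**Working it through.** **1. Which patients are in which set**

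| Patient | Surgeon's knowledge of arm ({11a} order) | ITT | mITT |
|---|---|---|---|
| Fails an intraoperative criterion, or no leak at second PEEP test | Blinded | Out | Out |
| Eligible, leak confirmed, unblinded, no study device applied | Unblinded | Out | Out |
| Unusable patch replaced by another patch or a control sealant | Unblinded | In, randomised arm | In if evaluable |
| Device touches dura, then leaks at third PEEP test | Unblinded | In | In, counted as failure |

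Only the second row combines knowledge of the arm with removal from every set. The per-protocol analysis does not restore it, since it removes subjects with deviations and adds none.

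**2. The plan's sample size**

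Inputs from Sample size {14}: success 91% in both arms, margin 10 points, one-sided 5%, power 80%, attrition 10%.

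n per arm = (1.645 + 0.842)² × 2 × 0.91 × 0.09 / 0.10² ≈ 101.3, so 102. Then 102 / 0.90 = 113.3, so 114 per arm and 228 in total. The stated figure reproduces. This point does not change it.

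**3. How much a few patients can matter**

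The number lost between unblinding and contact is not given. Assumed at 1 to 3% of 228, it is 2.3 to 6.8, or 2 to 7 patients.

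Upper Wald limit for the difference in failure rates, with 114 × 0.90 ≈ 103 evaluable per arm:

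- 12 v 9 failures: 0.0291 + 1.645 × √(0.1165 × 0.8835/103 + 0.0874 × 0.9126/103) = 0.0291 + 0.0693 = 9.8%. Passes.
- 13 v 9 failures: 0.0388 + 0.0707 = 10.9%. Fails.
- One omitted LIQOSEAL patient restored as a failure, 13/104 v 9/103: 0.0376 + 1.645 × √(0.1250 × 0.8750/104 + 0.0874 × 0.9126/103) = 0.0376 + 0.0703 = 10.8%. Fails.

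This shows that the threshold can turn on one patient. It says nothing about how often that would happen.

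A second illustration takes 102 per arm with the true difference at the margin (81% v 91% success) and assumes that k LIQOSEAL failures, and nobody else, are removed. The LIQOSEAL failure rate becomes (19.38 − k)/(102 − k). The chance of wrongly declaring non-inferiority is then:

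| k | Apparent difference in success | One-sided error |
|---|---|---|
| 0 | −10.0 points | 5% |
| 1 | −9.2 | 7% |
| 2 | −8.4 | 10% |
| 3 | −7.5 | 13% |

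These errors apply only if the loss is fully selective, which is an assumption.

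**4. When blinding ends**

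{11a} places unblinding after the second PEEP test. {17a} and {17b} place it when primary closure is final, a step that precedes that test. Read literally, the latter would let the leak test, and the criterion on the remaining gap after closure, be judged with the arm known. The criterion on whether LIQOSEAL can cover the opening has no stated time of judgement.

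**5. Blocks of 4**

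Over the six sequences of two A and two B, the best guess at positions 1 to 4 is right with probability 1/2, 2/3, 2/3 and 1, a mean of 70.8%. The allocation is certain with probability 0, 0, 1/3 and 1, a mean of 33.3%. Both figures require every earlier allocation in the stratum to be known. If an assumed 10%, 30% or 50% of patients are excluded before the surgeon sees their arm, certainty falls to about 27%, 16% or 8%, and correct guesses to about 68%, 64% or 60%.

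**The case against.** The strongest case against is that little is actually lost. Someone other than the surgeon randomises, the device waits in an opaque box, and on the {11a} order all eligibility testing is over before unblinding. Exclusions made blind reduce numbers but do not bias the comparison. Most application failures are kept: a patch that touches the dura and leaks at the third PEEP test is a primary-endpoint event, and a patient given either study device meets the contact rule and stays in the randomised arm. What remains is the short interval between unblinding and first contact, and nothing in the article suggests that it is often where patients are lost.

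All of this stands, and it limits the point. A reader might infer from exclusion after randomisation that the whole comparison is broken, or that every application failure of the patch vanishes. The documents support neither. A reader might also take the 71% guess rate as the operating figure; it is an upper bound, a guess would still have to alter an eligibility decision, and the PEEP tests are recorded on video.

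It can also be said that the comparison of withdrawal reasons between arms ({18b}) and the unseen full documents cover the rest. A listing of exclusions may indeed be planned there. But the article states the ITT definition itself, and that definition leaves these patients out whatever else is reported.

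**Conclusion.** The point holds in a limited form. The ITT set is a treated set. Its defining event follows unblinding on the article's own order, and the primary and safety sets inherit the rule. The supplementary ITT analysis therefore cannot check the primary result for selective loss at that step. The size is unknown and may be small; the 2 to 7 patients and the error rates of 7 to 13% rest on assumed losses, the latter on fully selective ones.

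The consequence for safety is narrower than for efficacy, because a patient who received no device cannot have an effect from one.

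That exclusions before unblinding are harmless depends on blinding lasting through the second PEEP test, on which {11a} and {17a}/{17b} differ. The fixed block size is a secondary weakness and does not carry the finding.

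**What to change.** 1. Define ITT as every randomised patient who met the intraoperative criteria and leaked at the blinded second PEEP test, analysed as randomised whether or not a device reached the dura. Rename the present set as treated. The mITT primary analysis can stay as it is.
2. Include patients with no device application in the ITT analysis. Four of the five endpoint components (deep or organ-space infection, percutaneous leak, and the two pseudomeningocele criteria) can still be observed to day 90. Add a sensitivity analysis that counts these patients as failures. Keep it as a sensitivity analysis, because the intraoperative component is defined as leakage after device application and some patients may go untreated for reasons unrelated to the device.
3. Report all post-randomisation exclusions by arm and reason, separating those before unblinding from those after.
4. Reconcile {11a} with {11c}, {17a} and {17b}, so that every intraoperative eligibility decision, including device coverage, is settled and recorded before the surgeon is unblinded.

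Cost: a sentence or two on the sets, one sensitivity analysis, one table, and 90-day follow-up of any untreated patients. The drawback is that a few patients without a post-application leak test enter the supplementary analysis. The sample size is unaffected. Changing block sizes or the time of randomisation during recruitment is debatable and is not needed for this fix.
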